3.2.2.3　Basis for establishing inclusion and exclusion criteria

Inclusion criteria

1: The target age for this clinical trial is not specified.

However, data collection for pain and QOL assessment will not be mandatory for patients aged 5 years or younger at the time of consent, as it is considered difficult to assess pain and QOL, which are part of the secondary endpoints. In the case of patients under 5 years of age, the Coordinating Committee will evaluate the appropriateness of inclusion or exclusion in advance.

4: In the field of plastic surgery in Japan, the size classification for tumor resection covered by insurance is 20 mm for the head and neck region and 30 mm for the extremities and trunk, and the same classification is used in actual clinical practice. In addition, the size at which detailed evaluation of venous malformation volume reduction or regression is possible on MRI is 20 mm or larger. Therefore, we judged it appropriate to set the target lesion size at 30 mm or larger in long diameter for the extremities and trunk and 20 mm or larger in long diameter for the head and neck.

2, 3: To select subjects who meet the objectives of the study, as well as to comply with GCP and ensure the safety of the subjects

5: Because it is difficult to evaluate images and determine effectiveness of treatment.

Exclusion criteria

1-7, 9-12: To take into account the safety of the subjects and to eliminate unexpected influences on the study results

8: To ensure the safety of the subject. However, when performing sclerotherapy for venous malformations, it is necessary to prepare the drug with an angiographic X-ray contrast medium. Therefore, if the patient is allergic to a specific contrast medium, it is necessary to select a different contrast medium that is usable (does not cause allergy) for the patient. The measures above are considered acceptable from a risk-benefit perspective since the subject is a patient who has no treatment options and whose ADL has declined due to pain and other symptoms deriving from the lesion.

4. Treatment

4.1　Investigational drug

4.1.1　Source

The investigational drug will be provided by Fuji Chemical Industry Co., Ltd.

Please refer to "Appendix 1: 1.13 Investigational Drug Provider" for the person responsible for providing the investigational drug and contact information etc.

4.1.2　Feature

The characteristics of the investigational drug are as follows

Ingredient symbol: FO-611

Nonproprietary name: Monoethanolamine oleate

Dosage form: liquid/injection

Content: 1.000 g monoethanolamine oleate (0.822 g oleic acid, 0.178 g monoethanolamine) in 1 vial (10 g)

Description: Clear, viscous, colorless to pale yellow injectable liquid

Route of administration: intravenous (direct puncture into lesion)

4.1.3　Packaging and labeling of investigational drug

The investigational drug is contained in a vial and housed in an outer box. The outer box has a label indicating that the drug is investigational use, the identification code, protocol number, serial number, storage method, shelf life, and the name, affiliation, title, and address of the Coordinating Committee (chairman).

A sample of the labeling is shown in the figure below.

For Clinical Trials

FO-611

Protocol No.: EO-1

Serial number: P032A

Storage: Room temperature

Shelf life: 3 years

Coordinating Committee:

Kobe University Hospital, Department of Plastic and Reconstructive Surgery

Special Lecturer, [name]

[name]

4.1.4　Preparation methods and considerations

The following procedure is used to prepare the investigational drug.

1. Remove the flip-off cap of the vial of the investigational drug and clean the surface of the rubber stopper with alcohol cotton.
2. Take 10 mL of water for injection or angiographic X-ray contrast medium as a diluent in a syringe, and inject it into the vial by inserting a needle vertically into the center of the rubber stopper (20 mL volume after preparation).
3. After injection, shake the investigational drug horizontally to confirm that it is uniformly dissolved before use.

Suitability as a diluent is as follows

| Type of diluent | | Suitability as a diluent |
| --- | --- | --- |
| water for injection | | Suitable |
| physiological saline solution | | Unsuitable*. |
| X-ray contrast media for angiography | Iopamidol formulation (iodine content: 300, 370 mg/mL) | Suitable |
|  | Iohexol formulation (iodine content: 300, 350 mg/mL) | Suitable |
|  | I Oxaglic Acid Preparation | Unsuitable*. |
|  | Ioversol formulation (iodine content: 320, 350 mg/mL) | Unsuitable** |
|  | Iomeprol formulation (iodine content: 300, 350, 400 mg/mL) | Suitable |
|  | Iopromide preparation (iodine content: 300, 370 mg/mL) | Unsuitable** |

*: Do not use because it may become cloudy or not reduce viscosity.

**: Do not use as it may become cloudy.

The solution is a clear, viscous, colorless to pale yellow injectable solution.

The shaking during preparation causes minute air bubbles to be dispersed in the solution. After 1-3 minutes of standing, the air bubbles will collect on the surface of the solution. Aspirate the solution into a syringe, taking care to avoid air bubbles on the surface.

This product should be used immediately after mixing with water for injection or angiographic X-ray contrast medium. To avoid bacterial contamination, preparation should be done immediately before use, and residual liquid after use should not be reused.

4.1.5　Concentration of solution after preparation

Each vial (10 g: 10% ethanolamine oleate) is dissolved in 10 mL of water for injection or angiographic X-ray contrast medium, to make a solution concentration of5% ethanolamine oleate. The total volume after preparation will be 20 mL.

4.1.6　Dosage and administration

Inject 5% ethanolamine oleate directly into the lesion at a maximum dose of 0.4 mL/kg. The same method of administration is used for children (under 15 years of age). However, the maximum dose per treatment should be 30 mL (as prepared drug solution).

[Method of calculating the maximum dose (mL)]

(1) Measure the subject's body weight (kg) (to the first decimal place). If the second decimal place can be measured, it shall be rounded off and calculated to the first decimal place.

(2) Calculate the maximum dose (mL) using the following formula based on body weight. Round off the second decimal place and calculate to the first decimal place.

Maximum dose (mL) = 0.4 (mL/kg) x body weight (kg) <up to 30 mL>

4.1.7　Pre-treatment

Considering the use of contrast and sclerosing agents, 5-10 mL/kg of supplemental fluid should be administered prior to sclerotherapy.

4.1.8　Sclerotherapy procedure

Sclerotherapy is performed according to the following procedure

- 1. In principle, general anesthesia using inhalation anesthesia should be administered to children (under 15 years of age). However, if the weight (physique) and pathological conditions of the patient are taken into consideration and it is judged that there is no problem, the same anesthesia method as that for adults may be used.

For adults (15 years of age and older), general anesthesia with anesthetics such as propofol and/or inhalation anesthesia should be used. It is also possible to perform the procedure under local anesthesia.

- 1. The target lesion is confirmed using echosonography or other means and punctured directly with a 22-25 G needle. Confirm that the puncture is made intravenously by checking for reverse bleeding.
  2. Inject contrast medium and check the morphology and circulation of the lesion under Digital subtraction angiography (DSA) or fluoroscopy. Check for misinjection or problems of the outflow pathway.
  3. Once safety is confirmed, the sclerosing agent is injected.
  4. If there are areas within the target lesion where the sclerosing agent has not been injected sufficiently, repeat operations (2) to (4).
  5. The treatment is terminated when it is determined that the sclerosing agent has been successfully injected into the target lesion.
  6. Check the skin tone and if it is determined that there is a problem with skin perfusion, a steroid-containing ointment should be applied.
  7. If necessary, use surgical tape or elastic bandages to compress the area of treatment.
  8. The day after the sclerotherapy, release the compression and check the skin tone and lesion. If necessary, reapply compression.

4.1.9　Post-treatment

Ointment (even steroid-containing ointment) or intravenous steroids should be administered to reduce swelling in the treated area if necessary. Surgical tape or elastic bandages should be applied for compression for approximately 2 weeks.

4.1.10　Additional treatment

For patients with diffuse lesions (when the target lesion is a diffuse lesion), and there is little improvement in symptoms such as pain after 4 weeks from the initial treatment (when there is almost no change in VAS [Visual Analogue Scale] or when an exacerbation is observed), and the investigator or subinvestigator determines that additional treatment is necessary, additional treatment may be performed once within 3 months (whether or not additional treatment is necessary is determined at least 4 weeks after the initial treatment). The dosage and administration of the additional treatment should be the same as that of the initial treatment. If additional treatment is conducted, the efficacy and safety is evaluated 3 months after the additional treatment.

4.1.11　Duration of a drug administration

Single dose. However, if the target lesion is a diffuse lesion, additional treatment may be performed once if necessary.

4.1.12　Criteria for discontinuation of investigational drug

Discontinue the investigational drug if any of the following occur during administration of the investigational drug

1): Skin necrosis

If skin pallor is observed starting administration of the investigational drug, arterial embolization should be suspected and the administration should be discontinued immediately.

2): Immediate allergic reaction (anaphylaxis, etc.)

If an immediate allergic reaction related to the investigational drug is suspected, such as a widespread rash or hemodynamic disruption , administration of the investigational drug should be discontinued immediately.

4.1.13　Storage conditions for investigational drug

The investigational drug should be stored in the packaging provided by the investigational drug provider in accordance with the storage conditions indicated on the investigational drug label. Storage temperatures must be recorded.

Details on the conditions of the investigational drug storage conditions are separately stipulated in the "Procedures for Management of Investigational Drugs".

4.1.14　Investigational drug management

The investigational drug manager shall receive the investigational drug supplied by the investigational drug provider after ensuring that the following conditions are met

- The investigational review board (IRB) has approved the protocol for this clinical trial
- Notification to the regulatory authorities has been accepted.

The investigational drug manager at the site must record the status of investigational drugs received, inventory at the site, delivery to each subject, and return or disposal of unused investigational drugs. The date, quantity, serial number, expiry date, etc. must be included in these records.

The investigational drug manager must record that the investigational drug specified in the study protocol has been appropriately delivered to the subject, and shall check for consistency of the quantity of the investigational drug received from the investigational drug provider.

Details of the procedures for the management of investigational drugs are separately stipulated in the "Procedures for the Management of Investigational Drugs".

4.1.15　Precautions for delivery of investigational drug and at the time of delivery

The investigational drug manager will deliver the investigational drug in accordance with the prescribing instructions of the investigator or subinvestigator.

4.1.16　Disposal of investigational drug

Since the investigational drug is essentially administered in a single dose in this study, no collection of the investigational drug unused will occur. Any residual of the prepared investigational drug (unused residual solution) should be disposed of at each site. Since this investigational drug is regulated as a "deleterious substance," the investigator, subinvestigator or the investigational drug manager should properly dispose of the residual liquid in accordance with the disposal procedures for "deleterious substances" at each site.

If the prepared investigational drug is not used at all for some reason, it should be disposed of according to the same procedure. In this case, the investigational drug manager must record the reason why the drug was not used in the investigational drug management table.

4.2　Concomitant medications/adjunctive therapies, restrictions, emergency procedures

The investigator and subinvestigator will record details of concomitant medications and concomitant therapies from the time of obtaining consent to the end of the observation period (up to 3 months after the administration of the investigational drug). If additional treatment is performed, the details of concomitant drugs and concomitant therapy until 3 months after the additional administration should be recorded in the case report form (CRF). The details to be recorded for the concomitant medications include the name of the drug, dosage, duration of administration, reason for use. For the concomitant therapy, the name of the therapy, duration of therapy implementation, reason for implementation.

4.2.1　Limitations on concomitant medications and concomitant therapies

In order to properly evaluate the effect of the investigational drug (monoethanolamine oleate), administration of the following medications; polidocanol, propranolol, Chinese herbal medicines (Kamishoyoshosan, Ginseng Yoeito, Ketsuyu Kaju-to, Kiki-Kenchu-to), and sirolimus; will be prohibited from the date of administration of the investigational drug until the end of the observation period (until 3 months after administration of the investigational drug, or until 3 months after additional administration in the case of additional treatment). However, in the case of additional treatment, the concomitant use of these medications is prohibited until 3 months after the administration of the investigational agent (until 3 months after the administration of the investigational agent).

4.2.2　Emergency medications, emergency procedures, additional concomitant medications/adjunctive therapies

If any of the adverse events listed in “4.1.12 Criteria for discontinuation of investigational drug” are observed during administration of monoethanolamine oleate, appropriate measures such as discontinuation of monoethanolamine oleate administration may be taken based on the judgment of the investigators and subinvestigators.

Any additional treatment (including blood transfusion, etc.) deemed necessary for the subject's health condition may be performed based on the judgment of the investigators and subinvestigators.

If hemolysis (gross hematuria) is observed, the patient should be treated with haptoglobin, if necessary, until the gross hematuria disappears. For adults (15 years of age and older), the initial dose is 2,000 units administered as a slow intravenous infusion. If symptoms do not improve, repeat doses may be administered as needed. The dosage may be adjusted according to the patient's age and body weight. The usual dosage for children (under 15 years of age) is 2,000 units per dose.

5.　Observation items and evaluation

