1.1　Medical background

1) About Venous Malformations

Venous malformation is an abnormality in the formation of vascular vessels during the embryonic period and is associated with symptoms such as pain and movement disorders. The estimated number of patients in Japan (Ministry of Health, Labour and Welfare's Research and Study on Intractable Hemangioma, Hemangiopericytoma, Lymphangioma, Lymphangiomatosis and Related Diseases, Ministry of Health, Labour and Welfare's Research and Policy Project on Intractable Diseases in Fiscal 2014) is approximately 20,000. Half of the estimated 20,000 possess lesions which are considered to be difficult to resect, such as extensive cases or cases with muscle involvement^1)^, and sclerotherapy is the treatment of choice for these patients (number of applicable patients: approximately 10,000).

2) History of the development of this product for venous malformations

In Japan, ethanolamine oleate, anhydrous ethanol, and polidocanol are used in off-label sclerotherapy. Regarding safety, ethanolamine oleate is considered a safe sclerosing agent with few side effects and no serious side effects as shown in a systematic review by Horbach et al (venous malformation or lymphatic malformations) compared to anhydrous ethanol, and polidocanol in which life-threatening side effects have been reported (Jo JY, et al: Cardiovascular collapse due to right heart failure following ethanol sclerotherapy, Frost et al: A case of a child with two cardiac arrests during polidocanol vascular sclerotherapy)^2, 3)^. In 5 studies 188 patients with venous malformations or lymphatic malformations, skin ulceration and skin necrosis [6 cases, 3%] were observed as side effects, but no systemic side effects, facial neuropathy, or other side effects were reported)^4)^. In a study that evaluated the cytotoxicity of each sclerosing agent on muscle tissue, ethanol was the most cytotoxic, with ethanolamine oleate and polidocanol being comparable.^5)^ Efficacy was also reported with ethanolamine oleate showing reduction of lesions and improvement of symptoms in 88-100% of cases^4)^. 83 other cases (85 operations) in which ethanolamine oleate was administered mainly to children (average age 15.1 years: 3 months to 21 years of age) reported complete remission of symptoms in 79 lesions and significant improvement in 6 lesions.^6)^

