3.2.2.2　Exclusion criteria

1. Patients with multiple organ failure or DIC (Disseminated intravascular coagulation)
2. Patients who are taking or have taken drugs that may affect resolution of lesions (propranolol, herbal medicines [such as Kamishoyosan, Ninjinyoeito, Eppikajutsuto or Ogikenchuto], or sirolimus). However, patients can participate in the clinical study in case herbal medicines are discontinued 2 weeks or more before study drug administration.
3. Patients with diabetes mellitus with HbA1c>=8.0, or autoimmune disorder
4. Patients with hepatic dysfunction grade C (10-15 points) in Child-Pugh classification
5. Patients with renal dysfunction with eGFR < 60mL/min/1.73m2
6. Patients with cardiac dysfunction with over grade II in NYHA classification
7. Patients who received sclerotherapy within 6 months before obtaining informed consent
8. Patients with history of allergy to ethanolamine oleate or angiographic X-ray contrast agent as concomitant drugs
9. Patients who have undergone surgery longer than 45 minutes within 2 weeks before obtaining informed consent
10. Patients participating in other clinical study within 4 weeks before obtaining informed consent
11. Pregnant women, women who may be pregnant, or lactating women
12. Patients who are judged as inappropriate by investigator/subinvestigator

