7.1　Termination (discontinuation) of treatment of individual subjects

The investigator and subinvestigator will discontinue the administration of the investigational drug and discontinue this clinical trial for subjects who fall into any of the following categories. If an adverse event has occurred at the time of discontinuation, the investigator and subinvestigator will take appropriate measures for the adverse event and follow up the outcome of the adverse event to the extent possible, with a deadline of the end date of this entire clinical trial (scheduled last observation date for all subjects).

- The subject or surrogate withdraws consent for the administration of the investigational drug or for participation in the clinical trial (for any reason)
- If continued participation in the clinical trial is likely to endanger the subject
- When "4.1.12 Criteria for discontinuation of investigational drug " is applicable.
- If a subject is found not to meet the eligibility criteria
- If the investigator or subinvestigator determines that the subject or surrogate is unable to comply with the study protocol
- If the subject is unable to come to the hospital due to personal reasons on the subject's side (e.g., relocation, hospital transfer, etc.)
- If the subject becomes pregnant
- Other medical reasons (e.g., surgery, adverse events, other diseases, etc.) that make it impossible to administer the investigational drug
- When the investigator or subinvestigator determines that it is appropriate to discontinue the clinical trial for other reasons

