8.1　Analysis population

8.1.1　Definition of analysis population

The population to be analyzed is defined as follows.

(1) Full analysis set (FAS): all subjects who were administered the study drug

(2) Per protocol set (PPS): The subjects in the FAS, excluding those with the following serious violations of the study protocol regulations in terms of study methods, concomitant therapy, etc. The PPS will be set for the purpose of confirming the stability of the primary analysis for the efficacy endpoints.

・Inclusion criteria violation

・Exclusion criteria violation

・Significant deviations from the study protocol that could affect the evaluation of efficacy

(3) Safety analysis set (SAS): Same as FAS

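### The on-study list of prohibited treatments omits a rival sclerosant that the protocol itself names and any procedure on the target lesion, and the protocol has no rule keeping the resulting shrinkage out of the primary responder count

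*Protocol*

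**What the plan says.** **On-study restrictions.** Protocol section 4.2.1 is headed as covering both medications and therapies. Its stated aim is a sound evaluation of the study drug's effect. It provides that "administration of the following medications; polidocanol, propranolol, Chinese herbal medicines (Kamishoyoshosan, Ginseng Yoeito, Ketsuyu Kaju-to, Kiki-Kenchu-to), and sirolimus; will be prohibited" between dosing and the end of observation. Only drugs are listed.

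**Sclerosants in use.** Section 1.1 says: "In Japan, ethanolamine oleate, anhydrous ethanol, and polidocanol are used in off-label sclerotherapy".

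**Entry criteria (3.2.2.2).** Exclusion criterion 7 bars sclerotherapy in the 6 months before consent, whatever the agent. Exclusion criterion 2 uses open wording for herbal products: "herbal medicines [such as Kamishoyosan, Ninjinyoeito, Eppikajutsuto or Ogikenchuto], or sirolimus".

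**Other treatment.** Section 4.2.2 adds: "Any additional treatment (including blood transfusion, etc.) deemed necessary for the subject's health condition may be performed based on the judgment of the investigators and" …

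**Study dosing (4.1.11).** "Single dose. However, if the target lesion is a diffuse lesion, additional treatment may be performed once if necessary".

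**Analysis.** The primary endpoint (5.1.1) is a volume reduction of at least 20% at 3 months, with no condition about other treatment of the lesion. Section 8.1.1 defines "Full analysis set (FAS): all subjects who were administered the study drug", and 8.1.2 makes that set primary for efficacy. The per-protocol set removes eligibility violations and significant deviations that could affect efficacy. Discontinued subjects also have a 12-week MRI (6.2.4.2).

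**The concern.** In a single-arm trial there is no comparator to absorb the effect of other treatment. Attribution of shrinkage to the study drug rests on what subjects may receive between dosing and the 3-month MRI, and on how any breach is scored.

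The list does not do this consistently. If polidocanol threatens the evaluation, the protocol gives no reason why anhydrous ethanol does not. The entry rule covers sclerotherapy with any agent, whereas the on-study rule covers one agent, although on-study treatment bears more directly on the primary MRI. Despite the heading, no therapy or procedure is addressed.

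The gap carries into the analysis. Treatment that no rule forbids is not clearly a deviation, so the per-protocol set may not remove the subject. The full analysis set keeps every dosed subject. At stake is whether a cohort's success could rest on a lesion reduced by something other than the study drug.

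**Working it through.** **1. The passages side by side**

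| Treatment of the target lesion | Before entry | On study (4.2.1) |
| --- | --- | --- |
| Polidocanol | Barred for 6 months (exclusion 7) | Prohibited |
| Anhydrous ethanol | Barred for 6 months (exclusion 7) | Not listed |
| Ethanolamine oleate beyond the planned doses | Barred for 6 months (exclusion 7) | Not listed, but capped by 4.1.10 and 4.1.11 |
| Herbal medicines | Open wording (exclusion 2) | Closed list of four names |
| Excision or another procedure | No lesion-specific rule | Not listed |

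**2. Inputs for the test** (8.2.2.1 and 8.6): threshold 20%, expected rate 50%, one-sided level 0.025, exact binomial test, 19 cystic subjects before dropout, target 22 per cohort.

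**3. The plan's own figure.** For each n, take the smallest r with P(X ≥ r | n, 0.20) ≤ 0.025; power is P(X ≥ r | n, 0.50).

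- n = 18: r = 8, size 0.0163, power 0.760.
- n = 19: r = 8, size 0.0233, power 0.820.

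The stated 19 is reproduced as the first n to reach 80% power.

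**4. The rule at 22**

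- P(X ≥ 9 | 22, 0.20) = 0.0201: passes. Power at 50% is 0.857.
- P(X = 8) = 319,770 × 0.2⁸ × 0.8¹⁴ = 0.0360, so P(X ≥ 8) = 0.0201 + 0.0360 = 0.0561: fails.

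**5. Effect of other treatment on type I error.** Assume the true study-drug rate is 20% and that k subjects receive other lesion-reducing treatment. If all k count as responders, the error is P(X ≥ r − k | n − k, 0.20). For n = 22 and k = 1 this is P(X ≥ 8 | 21, 0.20) = 0.0431; for k = 2 it is P(X ≥ 7 | 20, 0.20) = 0.0867. The table also shows the case where each such subject responds with probability 0.5.

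| k | n = 22 (r = 9), all respond | n = 22, half respond | n = 19 (r = 8), all respond | n = 19, half respond |
| --- | --- | --- | --- | --- |
| 0 | 0.020 | 0.020 | 0.023 | 0.023 |
| 1 | 0.043 | 0.029 | 0.051 | 0.034 |
| 2 | 0.087 | 0.040 | 0.106 | 0.048 |
| 3 | 0.163 | 0.055 | 0.202 | 0.067 |
| 4 | 0.284 | 0.075 | 0.352 | 0.091 |

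Break-even for one subject at n = 22: let q be that subject's chance of being scored a responder. The error is q × 0.0431 + (1 − q) × P(X ≥ 9 | 21, 0.20), where the last term is 0.0144. Setting this to 0.025 gives q = (0.025 − 0.0144) / (0.0431 − 0.0144) = 0.37. Above about 37%, one subject is enough to exceed the planned level.

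**6. Cost of scoring such subjects as non-responders** (n = 22, true rate 50%). Power is P(X ≥ 9 | 22 − k, 0.50): 0.857 for k = 0, 0.808 for k = 1, 0.748 for k = 2.

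**The case against.** Several points on the other side are sound and limit the finding.

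- **Permission.** A reader might infer that 4.2.2 allows elective re-treatment of the lesion. It does not say so. Its heading concerns emergencies, its test is need for the subject's health, and its example is blood transfusion. The protocol is silent on anhydrous ethanol and excision, and silence is not permission.
- **Extra ethanolamine oleate.** A reader might infer that this is also open. It is not: 4.1.10 and 4.1.11 cap the doses, so more would be a deviation, recordable under 9.7 and open to per-protocol exclusion.
- **Surgery after discontinuation.** Section 7.1 mentions surgery only under "Other medical reasons (e.g., surgery, adverse events, other diseases, etc.) that make it impossible to administer the investigational drug". After a cystic subject's single dose no administration remains to prevent, and a subject never dosed is outside the full analysis set. The clause is weak support for a surgical route into the analysis.
- **Likelihood.** Inclusion criterion 3 requires lesions that are difficult to remove, which makes excision less likely. Section 1.1 links anhydrous ethanol to life-threatening side effects. No passage shows that poorly relieved subjects would receive either within 12 weeks.
- **Herbal names.** Both lists give four names in the same order, and the differences look like translation variants. Only the open-versus-closed wording is a real discrepancy.
- **Scoring.** Section 8.1.3 provides case review before the data are fixed, and the unseen SAP may hold a rule for such subjects. The lack of a scoring rule would not be a finding on its own.

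What remains is the list itself. Prohibited treatments are fixed by the protocol, and a SAP cannot repair them after the fact. Whether a case is a deviation depends on that list, and case review without a stated criterion, in an open-label trial, is a weak safeguard.

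**Conclusion.** The point holds in a limited form. The list in 4.2.1 is incomplete against the sclerosants named in 1.1 and narrower than exclusion criteria 2 and 7, and it addresses no procedure on the target lesion. Followed as written, the protocol would let shrinkage after such treatment count towards the primary result, with uncertain removal even from the per-protocol set. The documents do not support saying that it expressly permits such treatment, or that every such case would certainly be scored as a response.

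The consequence could be material because the counts are small: one subject separates 8 (fail) from 9 (pass) at n = 22. The type I error figures of 0.043 and 0.087 assume a true rate at the 20% threshold, 22 evaluable subjects, and one or two subjects whose response is certain because of other treatment. If response is only even odds, the figures are 0.029 and 0.040, still above 0.025. The number of such subjects is an assumption and may be zero. This should be corrected, but it does not invalidate the design.

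**What to change.** 1. Reconcile 4.2.1 with section 1.1 and exclusion criteria 2 and 7, so that the protocol says consistently how non-protocol treatment of the target lesion, by drug or procedure, is handled during observation. Use one set of herbal names and one form of wording. Which treatments to restrict is for the sponsor to decide.
2. State in 8.2.2.1 that a subject who receives any non-protocol lesion-reducing treatment of the target lesion before the primary MRI, including after discontinuation, is a non-responder in the primary full-analysis-set analysis.

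**Cost.** The change is protocol wording and one analysis rule. No new data are needed, because 4.2 already requires concomitant drugs and therapies to be recorded. The scoring rule withholds no care. The observed response rate may be slightly lower, and power falls as shown in step 6 of the working: by about 5 percentage points with one such subject (0.857 − 0.808 = 0.049) and 11 with two (0.857 − 0.748 = 0.109).
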